#### Primary outcome measure procedure

Before each assessment, radiographers will be provided with a guideline (see Table 3) for classification of radiographic examinations based upon a prior investigation.^27^ The anonymised DICOM (Digital Imaging and Communications in Medicine) images will be embedded into an image review software program (Codonics Clarity Viewer version 6.1, Middleburg Heights, Ohio, USA). Prior to interpreting and commenting on radiographs in the IIT, each participant will receive instruction on how to use this software to view each image. This software program has the capability to adjust image contrast/density, zoom, pan and invert an image as would be possible in clinical practice settings.

**Table 3 jmrs264-tbl-0003:** Examination classifications for primary outcome measure

Findings
Abnormal
1. Fractures
2. Joint disruptions
3. Joint effusions
4. Soft tissue swelling
Normal
1. Anatomical variants
2. Non‐traumatic pathology
3. Old fractures
4. Evidence of previous surgery

To simulate the clinical setting and typical workflow, the assessment will take place in a semi‐darkened room with a time restriction (a total of 90 min assigned to complete the assessment). The images will be reviewed using a standard personal computer monitor (2‐megapixels) that is consistent to reviewing images in the clinical setting. Neither a clinical history nor access to previous imaging for each examination in the IIT will be permitted. Not including clinical history is designed to ensure participant's responses to the IIT are entirely dependent on how well they scan and interpret the radiographic images, rather than an assessment of how well they interpret case histories in combination with radiographic images.

#### Secondary outcome measure

In addition to providing a description of the pathology (perceived to be) present for each examination, the participants will be asked to provide a ‘confidence rating’ to indicate how confident they are in their interpretation on a 5‐point Likert scale (normal, probably normal, possibly normal, probably abnormal and abnormal). These ratings will be reported at baseline and at follow‐up assessments.

Two questionnaires will also be administered (the first to be completed at the baseline assessment prior to randomisation, the second is completed at the 12‐week post‐intervention assessment). The content and format of the two questionnaires is comparable, with the exception of an additional question in the second questionnaire to investigate the participant's perception of the education format they received. These questionnaires will be completed via a secure web‐based platform. The development process for these secondary questionnaires followed recommendations for the design and conduct of self‐administered surveys for clinicians.^28^ The process involved forming a panel of local content and survey design experts who assisted in item generation, reduction and pretesting. Both electronic questionnaires were piloted with a small convenience sample of radiographers (*n* = 6). Questionnaire flow, format, interpretability, redundant items and overall length of questionnaires were assessed. Each questionnaire will be distributed to all participants via an email containing a hyperlink to the secure web‐based survey platform.

#### Sample size calculation

Owing to a lack of similar studies to inform effect size assumptions, the research team took a pragmatic approach to determining an appropriate effect size to use in the sample size calculation.^29^ The team consulted three medical imaging clinical educators to consider what they would classify as a meaningful difference in the primary outcome measure that would lead them to choose one education delivery format over the other. Their responses indicated that a difference of more than one correctly described image, which equated to 4 points or more on the IIT, would be considered a significant difference. Therefore, the target sample size will be 48 (24 participants per group). A sample size of 24 participants per group provides greater than 80% power^29^ to detect a 4‐point difference between groups in the primary outcome (IIT score) at a significance level of 0.05%, assuming a standard deviation of 4.5 and a dropout rate <15%.

### Statistical methods

Data analyses will be performed using Stata (StataCorp, College Station, TX, USA). Conventional descriptive statistics will be used to describe the sample (years experience as a radiographer, age, gender, current or previous involvement in a radiographer abnormality detection system, as well as the primary and secondary outcomes). Data will be analysed according to the intention‐to‐treat principles. Outcome measures will be compared within and between intervention groups at baseline, and follow‐up assessments using generalised linear models to determine whether there were differences between groups and changes in primary or secondary outcomes over time (group by time interaction). The primary time‐point of interest is the 1‐week post‐intervention assessment. From these analyses, it will be possible to determine which method of education delivery (if any) had a greater impact on improving the radiographers' ability to detect and describe abnormalities on trauma radiographs, with the opportunity to adjust for baseline confounders if indicated.

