## Methods/Design

### Study design

The Standard Protocol Items: Recommendations for Interventional Trials (SPIRIT) 2013 guidelines were used when preparing this study protocol.^20^ The study design is a multicentre, stratified (by years of experience) two group parallel‐arm single‐blind (assessor blinded) randomised controlled trial (Fig. 1). Participants will be allocated to one of the two groups: (1) intensive format of education or (2) non‐intensive format of education in a 1:1 ratio to examine whether either education delivery approach is superior to the other. Participants will undergo an assessment of their ability to interpret adult skeletal X‐rays, before education, at 1 week post‐intervention completion (primary time‐point) and at 12 weeks post‐intervention completion.

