### Randomisation

Computerised random number generation will be used to generate the randomisation sequence by a researcher not otherwise involved in the recruitment or assessment of participants. Participants will be stratified into four bands by years of clinical experience (1–2; 3–5; 6–12; 13 years+) to minimise the risk of differences in experience levels between groups. Concealment of allocation will occur through use of numbered opaque envelopes containing the group allocation for each participant and stored in a locked filing cabinet until the time of allocation. After a participant has completed their baseline assessment, an intervention co‐ordinator will be permitted to access the envelope with the corresponding participant number and open the envelope to reveal allocation (to either the intensive format or non‐intensive format). The baseline assessment will involve participants completing the primary and secondary outcome measures. This assessment will be conducted at the participant's place of work and scheduled in consultation with the participant and their manager to ensure their attendance.

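### The primary analysis does not condition on baseline IIT or the randomisation strata, and it leaves covariate adjustment open to choice after the data are seen

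*Protocol article*

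**What the plan says.** All references are to the protocol article.

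- **Randomisation:** "Participants will be stratified into four bands by years of clinical experience". The baseline test precedes allocation: "The baseline assessment will involve participants completing the primary and secondary outcome measures". Every randomised participant should therefore have a pre-allocation IIT score and a known band. Blocking within bands is not mentioned.
- **Statistical methods, model:** "Outcome measures will be compared within and between intervention groups at baseline, and follow‐up assessments using generalised linear models", with a group-by-time interaction for change over time. Baseline is thus a level of time in the model.
- **Statistical methods, time-point:** "The primary time‐point of interest is the 1‐week post‐intervention assessment".
- **Statistical methods, covariates:** the only provision is "with the opportunity to adjust for baseline confounders if indicated". Years of experience appears in that section only among the variables used to describe the sample.

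**The concern.** Three features of the stated analysis work against it.

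1. **Baseline IIT is not conditioned on.** With an unconstrained baseline, the group-by-time term estimates a difference in change. That is valid under randomisation, but less precise than a comparison adjusted for baseline. When the correlation between the two scores is below 0.5, it is also less precise than ignoring baseline altogether.
2. **The design controls for experience and the analysis does not.** If stratification balances the arms within bands and experience is prognostic, a model without the bands overstates the standard error.
3. **The adjustment rule sets no rule.** In a randomised trial, baseline imbalance arises by chance. Covariates belong in the model because they are prognostic or were stratified on, and should be fixed beforehand. As worded, the 1-week difference, the difference in change, and an adjusted form of either can all be read as the primary result.

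At stake are precision in a trial of 48 people and a single, identifiable primary answer.

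**Working it through.** **Inputs.** From Sample size calculation: difference 4 points, SD 4.5, 24 per group, power above 80%, dropout below 15%. Alpha is taken as 0.05 two-sided; the article prints it as a percentage, but 0.05 is the value that reproduces its sample size, and either format may prove superior. Assumed, because the article gives no figure: baseline-to-follow-up correlation r of 0.3 to 0.7, equal SD at both times, and bands explaining 10 to 30% of variance.

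**Step 1: the plan's own figure.** n per group = 2 × (1.960 + 0.842)² × 4.5² / 4² = 19.9, so 20. Dividing by 0.85 gives 23.5, so 24 per group and 48 in total. This matches. The calculation is an unadjusted comparison at one time-point. A t-test has 85.4% power at 24 per group and 79% at 24 × 0.85 = 20.4 per group.

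**Step 2: baseline IIT.** The effective SD is 4.5 × √(2(1 − r)) for change and 4.5 × √(1 − r²) for baseline adjustment. The variance ratio, change to adjusted, is 2/(1 + r). Power is from the noncentral t with noncentrality 4 / (SD × √(2/20.4)).

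| r | SD, change | SD, adjusted | Variance ratio | Power, 1 week only | Power, change | Power, adjusted |
|---|---|---|---|---|---|---|
| 0.3 | 5.32 | 4.29 | 1.54 | 79% | 65% | 83% |
| 0.5 | 4.50 | 3.90 | 1.33 | 79% | 79% | 89% |
| 0.7 | 3.49 | 3.21 | 1.18 | 79% | 95% | 97% |

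With no dropout (24 per group), change against adjusted is 72.2 against 88.5% at r = 0.3, and 97.3 against 98.8% at r = 0.7. Spending four further degrees of freedom lowers the adjusted figures by at most about 0.2 points.

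**Step 3: experience bands.** If arms are balanced within bands that explain a share R² of variance, the true standard error of the unadjusted difference is 4.5 × √(2(1 − R²)/24), while the model reports about 4.5 × √(2/24) = 1.30. At R² = 0.2 the true value is 1.16. Simulation with 48 participants in four bands of 12, balanced within bands (200,000 trials per scenario), gives:

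| R² | Type I error, bands omitted | Power, bands omitted | Power, bands included |
|---|---|---|---|
| 0.1 | 3.9% | 87% | 89% |
| 0.2 | 2.8% | 88% | 92% |
| 0.3 | 2.0% | 89% | 95% |

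With 1:1 allocation that ignores the bands, the unadjusted test stays at 5.0 to 5.1%.

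**Step 4: the open choice.** This is a worst case with no true difference, 24 per group and r from 0.3 to 0.7. If the smaller p-value were taken from the unadjusted 1-week and baseline-adjusted analyses, type I error would be about 6.4 to 8.5%. With the change contrast also available it would be about 9 to 10%.

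**The case against.** The strongest reply is that the plan is valid as it stands. Baseline IIT is already in the model as a repeated outcome, so a reader who infers that it enters only when adjustment is judged necessary would be wrong. Change and baseline adjustment are both legitimate in a randomised trial; the difference is efficiency. The stated power does not depend on adjustment, and the size of the gain rests on a correlation the article does not give. The same 60 cases are used at each assessment, so a high correlation, and hence a small gain, is plausible. All of this stands, and it limits the point to efficiency and prespecification.

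A reader might also infer a false-positive risk from omitting the bands. The documents do not support that: the effect is conservative, and it needs both balance within bands and a prognostic effect of experience, neither of which is documented. Nor does the article say that covariates will be picked by significance tests at baseline. Comparing outcomes at baseline may simply mean that baseline is a level of time in the model. The worst case in Step 4 shows what the wording permits, not what is planned.

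A covariate list may properly sit in an analysis plan that is not shown. That answers silence, but the article does not stay silent: it states a conditional rule based on confounding, and that rule is the problem.

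Finally, a model of the 1-week score alone would drop the 12-week comparison. This is a fair objection to too narrow a remedy, and the fix allows for it.

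**Conclusion.** The point holds as an improvement in efficiency and prespecification. It does not show that the planned analysis is invalid or that the trial misses its stated power. Baseline adjustment was better at every correlation examined: the gain over change is about 18 percentage points at r = 0.3, 10 at 0.5 and 2 to 3 at 0.7. If the primary estimate is the difference in change and r is as low as 0.3, power is below the stated 80% even without dropout. Omitting the bands costs roughly 2 to 6 points of power and makes the test conservative, on the assumptions of within-band balance and 10 to 30% of variance explained. The gains from baseline IIT and from the bands should not be added, because the baseline score may already carry much of what experience explains. The weakness of the adjustment wording depends on none of these assumptions.

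**What to change.** - Name one primary estimate: the between-group difference in IIT at 1 week, with baseline IIT (continuous) and experience band (the four randomisation strata) as fixed, prespecified covariates.
- Fit it either as an analysis of covariance or within a longitudinal model of the 1-week and 12-week scores, with baseline as a covariate or constrained equal between groups. The longitudinal form keeps the 12-week aim in the same model.
- Remove the conditional adjustment clause, and label any other adjusted analysis as a sensitivity analysis.
- Present baseline values descriptively, without between-group tests.
- State whether allocation is blocked within bands.

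The cost is wording and four degrees of freedom (one for baseline IIT, three for the bands). The data are already to be collected. Trial status reports that recruitment was under way at submission, so the change could be made before analysis.

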## Discussion

Errors in the interpretation of radiographs in the emergency department have important consequences for patients and clinicians.^5^ Failure to correctly identify abnormalities on radiographs in a timely manner may result in delayed or inappropriate treatment leading to suboptimal outcomes for patients and potential medicolegal claims against clinicians.^6^ Radiographer commenting has been proposed as a mechanism to reduce diagnostic errors by providing an immediate opinion on a radiograph at the time of image capture by the performing radiographer.^10^, ^12^, ^14^ The potential benefits of radiographer commenting are likely to be dependent on the radiographer's ability to detect and describe abnormalities when viewing and interpreting trauma radiographs. Consequently, access to effective training that radiographers receive in preparation for a radiographer commenting role is paramount. This will be the first randomised controlled trial to evaluate the effectiveness of intensive and non‐intensive formats of delivery of image interpretation education. This study will generate valuable evidence regarding how image interpretation education can be effectively delivered to radiographers in hospital settings nationally and internationally.

There are several limitations of this study that should be considered. The possibility of recall bias is always a potential limitation with studies that involve the completion of the same assessment during a relatively short time frame. To minimise participants memorising cases between assessments, this study will undertake two preventative actions. First, a minimum time period between any two assessments of 5 weeks will be employed. Second, a computer‐generated randomisation sequence will be used to present each 60 case assessment in random order, further limiting the potential for case recall. An additional limitation that is a risk when employing a voluntary sampling method for participation in a research study is the possibility of self‐selection bias. Radiographers who respond to the participation invite may have a greater interest in image interpretation education than non‐responders. Another potential limitation is that there was no pilot data to inform sample size calculations prior to the study commencement. If significant findings are not observed in the final analyses, a post‐hoc power calculation based on trial data will be conducted to inform planning for future studies. Furthermore, the knowledge and capabilities of rural radiographers in comparison to radiographers from metropolitan areas has not been contemplated in this study and may be considered a limitation of this trial which required participants to be available to receive either intervention format. Future research investigating their difference would be worthwhile.

Findings from this trial are likely to be of relevance to radiographers seeking image interpretation training as well as organisations providing image interpretation education to prepare clinical staff for participation in a radiographer commenting system. A further limitation of the trial is that the sample will be inclusive of radiographers, and findings may not be able to be directly extrapolated to other clinical disciplines (e.g. junior doctors, physiotherapists or nurse practitioners). Nonetheless, this trial will provide insight into how image interpretation education can be effectively delivered and pave the way for future research among other relevant health professions including physiotherapists, nurse practitioners and doctors who work in emergency department settings.

## Trial status

**Trial Registration:** Australian New Zealand Clinical Trials Registry – ACTRN12612000210875. The trial was recruiting at the time of submission.
